#### ***Grade 4: Life-Threatening Adverse Events***

Life-threatening adverse events include bone fracture or development of refractory myocardial ischemia, dyspnea, and clinically relevant contraindications for exercise as outlined by the American College of Sports Medicine. Study participants who develop Grade 4 adverse events will have their intervention discontinued permanently. The study participant will return for a follow-up evaluation as clinically indicated or in a maximum of 2 weeks and should remain under medical observation until the adverse event resolves or the study participant is stabilized.

#### **REPORTING SPECIFIC ADVERSE EVENTS**

All serious and/or unexpected adverse events regardless of causality will be reported within 48 hours (2 calendar days) of notification of the event to the Chair of the Institutional Review Board, and Chair of the Data Safety Monitoring Board. Deaths or life-threatening events related to study intervention will be reported within 24 hours of notification.

### Examples of IMPACT Study-Related Adverse Events

Examples of specific adverse events, which require immediate reporting include, but are not limited to the following:

1. Life-threatening adverse events
2. Inpatient hospitalization
3. Prolongation of an existing hospitalization
4. Disability
5. Occurrence of chest pain
6. Intermittent claudication
7. Cardiac or pulmonary complications as recommended by the American College of Sports Medicine
8. Any death that occurs while the patient is enrolled in the study including the follow-up period, or within 30 days of completing the study.

## 8.3 STUDY DISCONTINUATION

### 8.3.a EARLY DISCONTINUATION OF TREATMENT

If a study participant is removed from the study prior to completion of the intervention, the reason and date will be documented. If a study participant is removed from the study, the follow-up assessments will be obtained. If the study participant is removed because of intolerance or complications related to the intervention, the study participant would remain under medical observation until resolution or stabilization of the adverse event. Participants will be removed from the study for any of the following reasons:

- The study participant has a serious or life-threatening adverse event.
- The study participant develops serious illness.
- The study participant becomes pregnant during the study term.
- The study participant begins insulin therapy.
- The study participant enrolls in a clinical trial which interferes with study procedures and outcomes.
- The study participant suffers physical injury preventing the continuation of study intervention.
- The investigator feels that it is in the best interest of the study participant to withdraw.
- The study participant wishes to withdraw.
- The study participant fails to comply with the intervention protocol, assessments, or other requirements of the study.

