## 5.2 PARTICIPANT DISCONTINUATION

### 5.2.a PARTICIPANT DISCONTINUATION

The IMPACT study is based on voluntary participation. In other words, potential participants and study participants have the right to refuse participation and withdraw from the study at any time.

Circumstances may also arise where the study physician or nurse determines that a participant must withdraw from the study. Circumstances will be reviewed on an individual basis to determine if withdrawal from the study is to be temporary or permanent.

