#### Event Classification

Adverse events are categorized based on event outcomes.

1. Serious Adverse Event – Any event that results in the following outcomes: Death, risk of death (life-threatening), in-patient hospitalization or prolongation of hospitalization, a persistent or significant disability or incapacity, or congenital anomaly or birth defect.
2. Unexpected Adverse Event – Any adverse event, the specificity or severity of which is not an expected consequence of the medical treatment or procedure.

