#### ***Grade 3: Severe Adverse Events***

Severe adverse events include severe muscle soreness or stiffness that results in limited daily activity. Severe adverse events also include other physical events including, muscle strain, ligament injury, intermittent claudication, development of transient but reproducible dyspnea, chest discomfort, or lightheadedness. The intervention for study participants who develop Grade 3 adverse events will be modified until the adverse event returns to Grade 1 or less. More frequent evaluations may be required until the adverse event resolves or the study participant stabilizes.

If a severe adverse event persists despite a modified intervention, the intervention may be interrupted for up to a maximum of 2 weeks. If the intervention must be interrupted for more than 2 weeks, the participant may be permanently discontinued from the study. If the adverse event resolves within the 2 weeks, the modified intervention may be restarted. A study participant who tolerates the modified intervention for at least 2 weeks can then be increased to the full intervention.

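### The adverse-event grade rules and the removal list give different consequences for the same event, and stopping exercise is not separated from leaving the study

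*Protocol*

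**What the plan says.** **Removal list (Protocol 8.3.a, headed as early discontinuation of treatment).** "Participants will be removed from the study for any of the following reasons": nine bullets follow. The first is "The study participant has a serious or life-threatening adverse event". Others include starting insulin, an injury that prevents the intervention from continuing, and failure to comply with the intervention protocol, the assessments or other study requirements. The same section says that follow-up assessments will still be obtained after removal.

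**Grade 4 (8.2.b).** "Study participants who develop Grade 4 adverse events will have their intervention discontinued permanently". The participant is then re-evaluated and kept under observation. Removal from the study is not mentioned.

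**Grade 3 (8.2.b).** "The intervention for study participants who develop Grade 3 adverse events will be modified until the adverse event returns to Grade 1 or less". If the event persists, the intervention may be interrupted for at most two weeks. "If the adverse event resolves within the 2 weeks, the modified intervention may be restarted". For a longer gap: "If the intervention must be interrupted for more than 2 weeks, the participant may be permanently discontinued from the study".

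**Definition of serious (8.2.b, Event Classification).** It is defined by outcome, and one of the outcomes is "in-patient hospitalization or prolongation of hospitalization".

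**General withdrawal rule (5.2.a).** For withdrawal decided by the study physician or nurse: "Circumstances will be reviewed on an individual basis to determine if withdrawal from the study is to be temporary or permanent".

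**Analysis (6.2.a).** The opening of the data analysis plan treats participants who cannot or will not keep their randomised frequency as lost to follow-up. It limits the primary analysis to data gathered while on the assigned protocol, and calls this intention-to-treat. The Aim 1 statistical analysis text says participants are studied by randomised assignment.

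**The concern.** Two staff members who follow the protocol faithfully could handle the same injured or hospitalised participant differently, depending on whether they consult the grade rules or the removal list. That is a safety inconsistency, and a statistical analysis plan cannot cure it.

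The inconsistency also reaches the primary comparison. Some removal triggers depend on having an exercise intervention, which Arm 3 does not have, and starting insulin is linked to glycaemia, the basis of the primary outcome. If removal, or stopping exercise, ends the use of a participant's data, the exercise arms could be reduced to those who tolerated the sessions while usual care is not filtered in the same way. The comparison would then no longer be the one that randomisation protects.

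**Working it through.** The first six steps compare the text. Arithmetic enters only at step 7.

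1. **Life-threatening event.** The Grade 4 rule acts on the intervention. The first bullet of 8.3.a acts on study participation. A reader of 8.2.b alone keeps the participant in the study; a reader of 8.3.a removes the participant.

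2. **Grade 3 event that is also serious.** Grade measures severity and seriousness is defined by outcome, so one event can be both. Ligament injury is listed under Grade 3. If it leads to admission, it meets the definition of serious. The Grade 3 rule then permits modification, interruption, restart and a return to the full intervention, while 8.3.a requires removal. A Grade 3 event that is not serious does not meet this conflict.

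3. **Interruption beyond two weeks.** The Grade 3 rule leaves discontinuation from the study optional. If the cause is an injury that prevents the intervention from continuing, 8.3.a makes removal compulsory.

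4. **Staff-determined withdrawal.** Section 5.2.a allows a case-by-case decision and a temporary withdrawal. The list in 8.3.a is unconditional and has no temporary form.

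5. **Triggers by arm.** Of the nine bullets:
   - one can be met only in Arms 1 and 2 (injury preventing the intervention);
   - one is exclusive to those arms in part (non-compliance: the intervention element is, but assessments and other requirements bind Arm 3 too);
   - the remaining 9 − 1 − 1 = 7 can arise in any arm, including serious events, serious illness, pregnancy and insulin.

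6. **Route to the analysis.** Removal under 8.3.a does not itself discard outcomes, because follow-up assessments are promised. Exclusion comes from the opening of 6.2.a, which sets aside data gathered after a participant can no longer keep the assigned frequency. Usual care has no session frequency to fail, so this clause bears on the exercise arms. It contradicts the Aim 1 text on analysis by randomised assignment.

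7. **The plan's own figure that removals would affect (6.2.b).** With 92 per arm and 20% attrition, 92 / (1 − 0.20) = 115 per arm, and 3 × 115 = 345. Both stated figures reproduce. The same 20% is applied to every arm, with no allowance for triggers that differ by arm. The protocol states no expected removal rate, so differential loss cannot be calculated from it.

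**The case against.** The strongest reply is that this is loose terminology. Stopping the intervention and leaving the study can both happen, so the Grade 4 rule and 8.3.a could apply together. Severity and seriousness are different scales, so 8.3.a might simply add a rule for serious events. Section 5.2.a reads as a general provision, and 8.3.a has its own bullet for investigator judgement. The heading of 8.3.a and its promise of follow-up suggest that removal mainly means stopping treatment. Section 9.1.a also allows HbA1c to be taken from the health record when visits are missed.

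Part of this stands. The Grade 4 conflict is the mildest, since both actions could be carried out. But permission to restart is of no use to someone who must be removed, and an optional consequence is not a compulsory one. Neither section refers to the other or says which prevails. The reading of removal as merely stopping treatment would settle much of this, but the text does not say so.

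A reader might infer several stronger things that the documents do not support:

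- **That one event carries all three outcomes** (modify and restart, stop exercise, remove). Restart belongs to Grade 3 and permanent stopping to Grade 4; each conflicts separately with 8.3.a.
- **That several triggers are exclusive to the exercise arms.** Step 5 finds one wholly and one partly.
- **That loss must rise with dose, from Arm 3 to Arm 1 to Arm 2.** Sessions do differ (26 weeks × 1 = 26 against 26 × 3 = 78), but turning them into removal percentages needs a per-session risk that the protocol does not give. It would also count Grade 3 events as removals when the first response to them is modification. The rationale in section 1.2.a describes injury in the supervised model trial as very rare. Insulin starts can occur in any arm.
- **That the comparison is biased whatever the analysis.** Outcomes are still to be collected, so bias depends on whether the exclusion in 6.2.a is applied.
- **That sites would differ.** Group sessions are held at one location; the inconsistency is between staff members.

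**Conclusion.** The point holds as a set of pairwise contradictions between 8.3.a and, respectively, the Grade 4 rule, the Grade 3 rule for events that are also serious, the Grade 3 rule on long interruptions, and section 5.2.a. In addition, 8.3.a is headed as stopping treatment, acts as removal from the study, and then promises follow-up without saying which assessments or for how long.

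For the statistics, the conclusion is conditional. If the on-protocol restriction in 6.2.a governs the primary analysis, exercise-arm data can be excluded selectively. If analysis by randomised assignment governs and follow-up is completed, that route closes. No size or direction of effect can be given, because the documents contain no removal rate. The safety inconsistency rests on the wording alone and needs no assumption about rates.

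**What to change.** 1. Reconcile 5.2.a, the Grade 3 and Grade 4 rules in 8.2.b, and 8.3.a, so that each event has one stated consequence and any overlap between severity grade and seriousness is resolved explicitly. Which consequence applies is a clinical decision for the sponsor.
2. In 8.3.a, separate stopping the exercise intervention from leaving outcome follow-up.
3. State that the follow-up assessments already promised there are the remaining scheduled visits among V2 to V6, in all arms, unless consent is withdrawn.
4. Align the opening of 6.2.a with the Aim 1 analysis text, so that data collected after exercise stops are analysed by randomised arm.

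The cost is amendment wording and a small effort to keep stopped participants attending visits that are already planned.

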### 8.3.b STOPPING RULES

There is minimal risk for participating in this research study. Participation in physical activity may improve risk factors. The most likely scenario that would indicate a cessation of the study would be failure to recruit participants or implement the intervention as planned. However, in

addition to monitoring recruitment and compliance to the intervention, the IMPACT Study also monitors the rates of injury in study participants. The Safety Officer, in conjunction with the study investigators, will alert the National Institute of Health (NIH) and DSMB if a larger than reasonably expected injury rate occurs in the treatment groups. Other issues that are related to the stopping rules include:

1. New information – It is unlikely that new information will become available during this study that would result in discontinuing the trial.
2. Limits of assumption – It is possible that the value of data analysis will be limited by differences between the intervention groups at baseline or because of study drop-outs/or missing data. Baseline differences will be analyzed annually and effects on the power to detect differences in the outcome measures will be evaluated and discussed with the PI, Safety Officer, and the NIH. If the study dropout rate exceeds 15%, the Safety Officer will initiate a meeting with the PI to discuss strategies to increase retention. If the dropout rate exceeds 25%, the safety officer will meet with the study investigators to determine whether or not the study should continue.
3. Limit of rules – The IMPACT Study acknowledges that circumstances, other than what are listed, may justify stopping the study.

## **8.4 ADHERENCE TO ETHICAL, REGULATORY AND ADMINISTRATIVE CONSIDERATIONS**

### **8.4.a ETHICAL CONSIDERATIONS**

The IMPACT Study is responsible for obtaining IRB approval from Stanford University prior to study initiation. Study investigators will be responsible for submitting and forwarding reports to the IRB and DSMB.

#### **INFORMATION FOR PARTICIPANTS**

Before obtaining consent, participants will be informed of the objectives, benefits, risk and requirements of the IMPACT Study.

#### **Informed Consent**

All participants must provide their informed consent prior to any study visit activities. The written consent form will be the most current version that has been reviewed and approved by IRB. Informed consent will be obtained by the IMPACT study staff and the forms will be signed by the participants and the IMPACT staff who conducted the informed consent discussion. A copy of the signed forms will be made. The participants will have a copy of the form while the study will keep the original form in participant files.

### **8.4.b REGULATORY CONSIDERATIONS**

#### **FINANCING**

The IMPACT Study was funded by the National Institute of Diabetes and Digestive and Kidney Diseases (NIDDK) at National Institutes of Health (NIH).

**TRIAL REGISTRATION**

IMPACT has been registered on ClinicalTrials.gov as an efficacy study in February 2014. Its ClinicalTrials.gov identifier is NCT02061579.

**DISCLOSURE OF CONFLICT OF INTEREST**

Full disclosure by all of the key members of the IMPACT Study of their, and their immediate family's financial relationships with organizations just to have an active or potential interest in the conduct and outcome of the study. These are to be reported and reviewed annually.

## **Chapter 9: Data Collection and Management**

## 9.1 DATA COLLECTION

### 9.1.a PRIMARY AND SECONDARY DATA SOURCES

#### 8.1.a Primary and Secondary Data Sources

The IMPACT Study utilizes primary data sources for study research and analysis. IMPACT has designed and selected various collection tools to gather data for specific study needs. Secondary data sources are used only if data are missing from primary sources.

#### Primary Data Sources

Primary data sources are methods and tools utilized by IMPACT to collect information directly from its participants. This includes all participant information collected during or from:

- Telephone/online screenings
- Baseline study visits and subsequent study visits
- Paper and electronic surveys and questionnaires
- Exercise evaluation sessions
- Group exercise sessions
- Participant exercise logs

#### Secondary Data Sources

Secondary data sources are existing datasets collected by another entity. The IMPACT Study will use EpicCare EHR to obtain HbA1c results and other metabolic measurements if participants do not attend their study visits.

## 9.2 DATA MANAGEMENT

### 9.2.a REDCAP DATABASE

REDCap is a web-based application designed to build and manage online databases and surveys. REDCap is widely used at Stanford and has been approved for use on human subjects research studies.

The IMPACT Database is developed by the IMPACT study team. The database consists of a combination of data collection form and survey tools. The IMPACT Study is utilizing REDCap to store and manage study data

#### Data Entry

Collected study data is either entered directly into REDCap during study visits or entered into REDCap after being collected onto paper forms. The exact method of data entry will be determined according to resource availability and time efficiency.

### 9.2.b CONFIDENTIALITY AND PROTECTION OF PERSONAL HEALTH INFORMATION

To protect study participants, data will be strictly confidential. Only study team members and study-related personnel will have access to participant's private health information / health

information identifiers (e.g., first and last name, patient DOB, address and phone number) in order to schedule, run and conduct the study. Stanford University will share participants' identifying information and health information with the Cardiac Therapy Foundation only as necessary to conduct the study and to ensure participant safety.

All participants will be identified by a unique study ID, which will be generated as part of the study enrollment process. Data containing any identifying information such as a name or address will be kept separately from the study ID and other data collected for the study. Only the PI / study team will have access to the key code. No participant data will be stored on local drives or laptops.

Every effort will be made to keep identifying information confidential. Any printed materials containing information on participants (e.g., consent forms) will be stored in locked filing cabinets within locked offices, with access by the PI / study team only. No study participant will be identified individually in any publication. Participant names and identifiers will not be used in the publication or presentation of findings from this study.

Database development work, constructing data from multiple sources including primary data collection and entry, and EpicCare EHR, will be carried out by the SCCI/IMPACT analyst team. Database files will be maintained in a computer that will require passwords for access known only by study personnel. All data from study visits and intervention exercise sessions will be directly entered into the secure study database on a secure, password protected computer.

#### **9.2.c QUALITY CONTROL**

To ensure the quality of study data, IMPACT staff will be responsible for data checking and editing within a reasonable period of time. The IMPACT Study Coordinator will select and review a random selection of participant files quarterly for data entry accuracy and completeness.

